### Infections

All infections diagnosed by the investigator will be captured on specific infection CRF pages within the AE documentation chapter. The investigator will classify the severity (mild, moderate, severe, life-threatening, or fatal), type of infection (viral, bacterial, fungal, and other), and the seriousness of the infection (serious adverse event).

Opportunistic infections are defined as any CMV infection or viremia, BKV infection or viremia, or PJP.

### CMV

It is strongly recommended to provide prophylaxis and therapy measures for CMV according to the Third International Consensus Guidelines on the Management of Cytomegalovirus in Solid-Organ Transplantation (13 57)

CMV disease is defined as one or more of the following:

Fever > 38°C for at least 2 days;New or increased malaise;Leukopenia;≥ 5% atypical lymphocytes;Thrombocytopenia;Elevation of hepatic transaminases (ALT or AST) to 2 x the upper limit of normal;Evidence of CMV in blood by viral culture, antigenemia, or a DNA/RNA-based assay;No other cause of symptoms/signs identified.

Tissue-invasive CMV infections include symptoms/signs of organ dysfunction plus detection of CMV in affected tissue by culture, immunohistochemically analysis, or *in situ* hybridization. CMV-DNAemia is defined as asymptomatic (no CMV disease, no tissue invasive infection, or criteria of infection) CMV replication in blood

Assessment within the study:

Nucleic acid testing (NAT) will be performed at randomization, and months 6, 9, and 12 after transplantation for safety purposes;Additional monitoring of CMV DNAemisis due to the discretion of the investigator(s);Monitoring by NAT testing is strongly recommended in any case of suspected CMV infection.

All data on CMV DNAemia and infection will be documented in the eCRF.

*BKPyV vDNAeimia and BKPyV virus infection, and BKPyV nephropathy.* BK vDNAemmia is defined as the presence of elevated BK virus loads detected by standard NAT in the local laboratory. BKPyV virus infection is defined as clinical symptoms (e.g., elevated creatinine or BKV nephropathy) in the presence of BK viremia. BKV nephropathy is histologically proven BKV infection of the graft [17, 97]. In addition, BKPyV viremia as such and the degree of elevated creatinine will be recorded.

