### Leucocytopenia/Neutropenia

Leukopenia is defined as a leucocyte/neutrophil value below normal and/or the use of colony-stimulating factors. Within the final analysis, the incidence of low leucocyte values of < 4.0/nl, < 3.5/nl, < 3.0/nl, or < 2.5/nl will be determined throughout the study at and after randomization and at months 6, 9, and 12 post-transplant. The incidence of neutropenia < 1.5/nl will be determined throughout the study at and after randomization and at months 6, 9, and 12 post-transplant. The incidence of the use of colony stimulating factors will be determined throughout the study after randomization.

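### CMV disease, met by any one of eight items including CMV in blood alone, contradicts the definition of CMV-DNAemia and leaves that class empty

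*Protocol article*

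**What the plan says.** The CMV section of the protocol article sets the rule with "CMV disease is defined as one or more of the following" and then gives one list. Six entries are clinical or laboratory signs: "Fever > 38°C for at least 2 days;New or increased malaise;Leukopenia;≥ 5% atypical lymphocytes;Thrombocytopenia;Elevation of hepatic transaminases (ALT or AST"), the last with a cut-off of twice the upper limit of normal. Two further entries close the list: "Evidence of CMV in blood by viral culture, antigenemia, or a DNA/RNA-based assay;No other cause of symptoms/signs identified". No connecting word makes either of these two compulsory.

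The section then separates two other classes. For tissue invasion it says "Tissue-invasive CMV infections include symptoms/signs of organ dysfunction plus detection of CMV in affected tissue". For virus in blood alone it says "CMV-DNAemia is defined as asymptomatic (no CMV disease, no tissue invasive infection, or criteria of infection) CMV replication in blood". It schedules nucleic acid testing (NAT) at randomization and at months 6, 9 and 12 after transplantation for safety, and has all DNAemia and infection data entered in the eCRF.

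The text on BK virus under the same heading reads "BKPyV virus infection is defined as clinical symptoms (e.g., elevated creatinine or BKV nephropathy) in the presence of BK viremia". The Infections section says that infections are captured when the investigator diagnoses them, and adds: "Opportunistic infections are defined as any CMV infection or viremia, BKV infection or viremia, or PJP".

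**The concern.** The rule for CMV disease and the rule for DNAemia cannot both be applied. DNAemia requires that CMV disease be absent, yet the finding that defines DNAemia, virus in blood, is by itself enough for CMV disease. The scheduled NAT will pick up virus in patients without symptoms if it is there, and the printed rule would label every such patient as diseased.

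The rule also fails in the other direction. A patient with fever, malaise or a low leucocyte count and no CMV in blood meets it. So does a patient for whom the only satisfied entry is that no other cause was found, which has no meaning on its own.

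At stake is the reporting of a safety outcome: how many patients in each arm had CMV disease, and how many had asymptomatic viral replication. If the text does not say how the items combine, centres and analysts must each supply a rule.

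**Working it through.** The plan states no figure on this point, so there is nothing to reproduce. The check is one of logic.

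**Inputs** (all from the CMV section)
- Six signs: fever, malaise, leukopenia, atypical lymphocytes, thrombocytopenia, raised transaminases.
- B: evidence of CMV in blood.
- N: no other cause identified.
- Each of the eight items is present or absent, which gives 2^8 = 256 combinations. B is present in 2^7 = 128 and absent in 128.

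**Rule as printed: disease if at least one of the eight is present**
- Disease: 256 − 1 = 255 combinations. Only the combination with nothing present escapes.
- Disease without CMV in blood: 128 − 1 = 127 combinations, for example leukopenia alone or fever alone.
- CMV in blood: all 128 combinations are disease, so 128 − 128 = 0 remain for DNAemia.

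**Illustrative joint rule: at least one sign AND B AND N**
- Disease: 2^6 − 1 = 63 combinations, none without CMV in blood.
- CMV in blood but not disease: 128 − 63 = 65 combinations, so the DNAemia class is no longer empty.
- Of these 65, 2 have no sign at all (N present or absent). The other 63 have a sign for which N is not met. The article calls DNAemia asymptomatic, so a reworded definition must say where those 63 belong.

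These counts show which classes can exist. They say nothing about how often each combination occurs in patients.

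**Neighbouring definitions side by side**
- Tissue-invasive CMV: organ dysfunction together with detection of virus in the tissue. The link is explicit.
- BK virus infection: clinical symptoms together with viremia. The link is explicit.
- CMV disease: signs, virus and exclusion of other causes in one list, any entry sufficient. There is no link.

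The same section thus states a joint condition where it wants one. The CMV disease list is the exception.

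**The case against.** The strongest reply is that this is a layout or wording slip and not a chosen rule. Bullet lists elsewhere in the article, such as the eligibility criteria, have also been run together, and any sub-levels in the CMV list would be lost. The last entry refers back to the others and only makes sense as an added requirement, and the description of DNAemia as asymptomatic points the same way. This is plausible as to what was meant. It does not remove the conflict: the wording that makes any entry sufficient survives, and no conjunction appears.

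A second reply concerns the consequences, and most of it stands. Infections enter through investigator diagnosis (Infections section). Nothing in the article says that the list will be run against every patient's blood counts. Three stronger readings should therefore not be drawn:

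- **A heavy over-count of known size.** A reader might divide an assumed leukopenia rate by an assumed CMV disease rate. The document gives neither rate. The literal rule would also count the union of the groups, so the ratio would depend on an unknown overlap.
- **Double counting of leukopenia.** It has its own outcome ("Leukopenia is defined as a leucocyte/neutrophil value below normal and/or the use of colony-stimulating factors"), and it would remain both an outcome and a sign of CMV disease after any sensible rewording. That is no defect.
- **Bias from app reporting in the intervention arm.** Those patients document vital signs and wellbeing in the app, which could touch fever and malaise. The other four signs are laboratory values, and unequal reporting of symptoms would not disappear after rewording. Requiring virus would remove only the events without virus. The article does not show that a biased comparison would result.

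**Conclusion.** The contradiction is real and follows from the text alone. Under the printed rule DNAemia cannot occur, and a single non-specific sign without virus is CMV disease. The conclusion assumes only that the list is read as printed. If the full protocol nests the last two items as requirements, the fault lies in the article's wording alone.

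Its reach is limited to the CMV disease count and its separation from DNAemia. CMV is not among the seven primary indicators or the secondary endpoints listed under Study endpoints, and it does not enter the sample size. The opportunistic-infection outcome pools CMV infection and viremia, so moving a patient with virus between the two classes leaves that count unchanged. It would rise only if disease without virus were counted as CMV infection. No fold-inflation can be computed from the document.

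**What to change.** Reconcile the two outcome definitions before the CMV safety outcomes are analysed. One workable form:

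- **CMV disease:** evidence of CMV in blood, AND at least one listed sign or symptom, AND no other cause identified.
- **Tissue-invasive infection:** a separate class, as now.
- **CMV-DNAemia:** CMV in blood without CMV disease and without tissue-invasive infection, with a sentence on patients who have virus and a sign attributed to another cause.

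Apply this to the investigator-reported infections and the NAT results in the eCRF. Keep the exclusion of other causes as the investigator's judgement; a program cannot derive it unless it was recorded, and the article does not say that every sign has its own eCRF field.

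The cost is one reworded definition and a classification step on the recorded infection and NAT data, with a check of which items the eCRF holds. No treatment, visit or test changes. With last patient out expected on 30 April 2026 (Trial status), the rewording should be fixed before the CMV data are examined by arm.

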### Cardiovascular events

A cardiovascular major adverse cardiac event (MACE), stroke, or symptomatic peripheral artery disease is named MACCE (major adverse cardiac and cerebrovascular event) and defined as cardiac death, non-fatal MI, or coronary revascularization procedure. The history of all cardiovascular events will be captured at randomization and all cardiovascular events will be recorded throughout the study after randomization as AEs/SAEs. The estimated 7-year risk of major adverse cardiovascular events and mortality will be calculated according to Soveri et al. [86] according to age (years), creatinine (mg/dl), total time on renal replacement therapy (months), number of transplants, presence of coronary heart disease (yes/no), smoking status (previous (yes/no), current (yes/no), diabetes mellitus (yes/no), and LDL-cholesterol (mmol/l).

### Predict4Health (iBOX) survival probabilities

The iBox survival probabilities (33) will be generated using eight parameters, including baseline characteristics (time from transplant to evaluation), functional parameters (eGFR and protein/creatinine ratio), immunological parameters such as the presence of circulating anti-HLA donor specific antibodies, and histological parameters [biopsy findings including microcirculation inflammation (glomerulitis -g Banff score and peritubular capillaritis -ptc Banff score), interstitial inflammation and tubulitis (i and t Banff scores), transplant glomerulopathy (cg Banff score), and interstitial fibrosis/tubular atrophy (IFTA Banff score)]. To account for missing variables and allow adaptation at individual centers, derived probabilities will be generated using the diagnosis of ABMR, TCMR, BK virus-associated nephropathy, or recurrence of end-stage renal disease (ESRD) instead of Banff scores. Thus, three types of risk evaluation will be generated based on available parameters, which will allow flexibility across centers:

iBox#1: Functional (time from transplant to evaluation + eGFR + proteinuria) evaluation;iBox#2: Functional + immunological (DSA) evaluation;iBox#3: Functional + immunological + histological (biopsy) evaluation.

The iBox survival probabilities and evolution in time will give the clinician additional information to support their clinical decision to manage the patient. It is expected to give them earlier notice of any deviation or degradation in the allograft.

### Malignancy

Any malignant disease that occurs after transplantation will be recorded and the incidence will be calculated.

### Anemia

Anemia is defined as a hemoglobin value below normal and/or the use of erythropoietin-stimulating agents. The incidence of anemia will be determined throughout the study at and after randomization, and at months 6, 9, and 12 post-transplant. Within the final analysis, the incidence of low hemoglobin values <10g/dl or <11g/dl will be determined throughout the study at and after randomization, and at months 6, 9, and 12 post-transplant. Similarly, the incidence of the use of erythropoietin-stimulating agents will be determined throughout the study at and after randomization, and at months 6, 9, and 12 post-transplant.

### Leucocytopenia/Neutropenia

Leukopenia is defined as a leucocyte/neutrophil value below normal and/or the use of colony-stimulating factors. Within the final analysis, the incidence of low leucocyte values of < 4.0/nl, < 3.5/nl, < 3.0/nl, or < 2.5/nl will be determined throughout the study at and after randomization and at months 6, 9, and 12 post-transplant. The incidence of neutropenia < 1.5/nl will be determined throughout the study at and after randomization and at months 6, 9, and 12 post-transplant. The incidence of the use of colony stimulating factors will be determined throughout the study after randomization.

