### Method of assigning patients to the treatment groups

At the baseline visit, study personnel will register the patients, who will sign the ICF, in the database and will assign a unique patient identification number (PID number). The PID number will only identify the patient’s records. The investigator will keep a master patient list on which the PID number and the full name, address, and telephone number of each patient are listed.

For data collection, five study visits at the KTC are scheduled (months 0, 3, 6, 9, and 12). For the determination of tacrolimus trough level, two additional time points will be used (months 7.5 and 9.5). In addition, medication adherence, quality of life, and treatment satisfaction will be assessed by validated questionnaires.

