### Randomization

Randomization will be performed using a predefined variable block randomization scheme, stratified by the participating centers and the age of the participant. Due to low expected patient numbers in the age groups of < 12 years and 12 to 18 years, patients in these age groups will be randomly stratified by age, but not by KTC. The randomization scheme will be generated and reviewed by the study biostatistician and quality assurance staff and locked by them after approval. The investigation sites will assign eligible patients through an interactive internet-based computer system (IWRS) once a patient has satisfied the requirements to be included in the study. The IWRS randomization tool is part of the eCRF (Secutrial^®^, interActive Systems, Berlin, Germany). After screening for eligibility and assignment of the individual PID, each patient can only be assigned once to one of the treatment arms. Using the web-based tool will make it impossible for the study personnel to predict the assignment. The sites will record the time of randomization. Treatment in the assigned group starts in the first year after the kidney transplantation and ends in month 12 after randomization.

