### Baseline visit

At baseline (=visit 1), the patients will undergo routine medical examinations and central randomization will be performed to one of the two treatment groups in a 1:1 ratio. Different questionnaires will be assessed on paper or in electronic form. The established treatment will be continued until month 12, when the last control assessment will be performed. Investigators will be instructed to change immunosuppression only if necessary and based on clinical grounds. For any change in the immunosuppressive regimen, the investigator should explain this in the eCRF.

After the baseline visit, there will be four additional study visits during the 12-month treatment period.

Visit 2: 3 months ± 14 days after baseline

Visit 3: 6 months ± 21 days after baseline

Visit 4: 9 months ± 21 days after baseline

At the visits, 2–4 regular safety assessments (AEs/SAEs and AEs of special interest) and documentation of medication, BPAR, graft loss, and death will take place. The visit plan in section 4.7 shows the items to be evaluated at each time point. The different questionnaires will be assessed on paper or in electronic form. Most importantly, all visits and physician contact at the KTC, with the home nephrologists, the emergency unit, or admission to any hospital will be documented.

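### Fixed-time anaemia and leukopenia incidences are counted from transplantation, while entry is staggered and visits run from baseline, so these points can precede randomization and mostly miss a study visit

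*Protocol article*

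**What the plan says.** **Entry and trial period.** The inclusion criteria admit patients transplanted within the previous 12 months. The Randomization section states: "Treatment in the assigned group starts in the first year after the kidney transplantation and ends in month 12 after randomization".

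**Visits.** In the section on assigning patients to groups, "five study visits at the KTC are scheduled (months 0, 3, 6, 9, and 12"). The Baseline visit section counts them from baseline: "Visit 2: 3 months ± 14 days after baseline", "Visit 3: 6 months ± 21 days after baseline" and "Visit 4: 9 months ± 21 days after baseline". The month-12 visit is the last one; the article prints no window for it.

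**Fixed time points for blood counts.** In the Leucocytopenia/Neutropenia section, the incidences of low leucocyte values and of neutropenia "will be determined throughout the study at and after randomization and at months 6, 9, and 12 post-transplant". In the Anemia section, the incidences of anaemia, of low haemoglobin and of use of erythropoietin-stimulating agents "will be determined throughout the study at and after randomization, and at months 6, 9, and 12 post-transplant".

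**CMV testing.** The CMV section says: "Nucleic acid testing (NAT) will be performed at randomization, and months 6, 9, and 12 after transplantation for safety purposes".

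**Other outcomes.** De novo donor-specific antibodies at month 12 and HbA1c elevation at month 12 are both counted from randomization. Nothing in the article maps post-transplant months to study visits.

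**The concern.** Two clocks are in use, and they differ by each patient's time from transplantation to entry, which can be anything up to 12 months.

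- **Late entrant, month 10.** Months 6 and 9 post-transplant passed 4 months and 1 month before randomization. Month 12 post-transplant is study month 2. No fixed point lies in the remaining 10 study months.
- **Early entrant, month 1.** The three points fall at study months 5, 8 and 11. Each is about 30 days before a scheduled visit, and the printed windows at months 6 and 9 are only ± 21 days.

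The label month 12 post-transplant thus means 2 months of intervention for one patient and 11 months for the other. A value taken before randomization cannot have been affected by the intervention. A point with no matching visit either goes unmeasured or depends on whatever laboratory result happens to be nearby. The fixed-time incidences would then mix very different exposures, with a post-randomization denominator that changes from one time point to the next.

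**Working it through.** The article gives no figure on this point to reproduce, so the check is of the time axes.

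**Inputs.** Let U be months from transplantation to randomization, between 0 and 12 (inclusion criteria). Visits are at study months 0, 3 (± 14 days), 6 (± 21 days) and 9 (± 21 days), from the Baseline visit section. For month 12, ± 21 days is assumed. Baseline is taken as the exact day. One month is 30.44 days, so ± 14 days spans 0.92 months and ± 21 days spans 1.38 months.

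**Rule.** Month k post-transplant falls at study month k − U. It precedes randomization if U > k. It matches a visit only if k − U lies inside a window.

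**Uniform entry over 0 to 12 months (assumed).**

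- Before randomization: (12 − 6)/12 = 50% for month 6; (12 − 9)/12 = 25% for month 9; 0% for month 12.
- Inside a window, month 6: study time after randomization runs from 0 to 6, which covers the whole month-3 window and half of the month-6 window. (0.92 + 0.69)/12 = 13%.
- Inside a window, month 9: (0.92 + 1.38 + 0.69)/12 = 25%.
- Inside a window, month 12: (0.92 + 1.38 + 1.38 + 0.69)/12 = 36%.
- Between visits: the remainder, 37%, 50% and 64%.
- No matching study visit (before randomization or between visits): 87%, 75% and 64%.

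At month 12 post-transplant, mean time since randomization is E(12 − U) = 6 months, with individual values from 0 to 12.

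**Other assumed entry patterns** (percentages for months 6 / 9 / 12 post-transplant):

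| Entry, months after transplantation | Before randomization | Between visits |
|---|---|---|
| Uniform 0–3 | 0 / 0 / 0 | 62 / 54 / 54 |
| Uniform 0–6 | 0 / 0 / 0 | 73 / 58 / 54 |
| Early-skewed, Beta(1,3) on 0–12 | 12.5 / 1.6 / 0 | 58 / 57 / 54 |
| Uniform 0–12 | 50 / 25 / 0 | 37 / 50 / 64 |
| Uniform 6–12 | 100 / 50 / 0 | 0 / 42 / 73 |

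In every pattern tried, more than half of the points at each time fall before randomization or between visits. Allowing ± 14 days around baseline under uniform 0–12 entry lowers the unmatched shares only to 83%, 71% and 60%.

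**After re-anchoring.** Months 6, 9 and 12 after randomization are visits 3, 4 and 5 for every patient, so by design none precedes randomization and none falls between visits.

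**The case against.** Much of the case on the other side stands.

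- **Follow-up is not lost.** A reader might infer that the later part of follow-up is left out for many patients. The same sentences also call for incidence throughout the study at and after randomization, which covers all follow-up whenever a patient enters. Use of colony-stimulating factors is defined only over the study after randomization. The problem is confined to the fixed time points.
- **A distorted arm comparison is not shown.** The article says only that incidences will be determined. It does not say that values from before randomization enter a comparison between arms, and how such values are handled could well be left to an analysis plan. Randomization should also balance entry time between arms on average.
- **CMV is not a fixed-time outcome here.** The cited sentence is a testing schedule for safety. The section also allows further monitoring, recommends testing whenever infection is suspected, and has all CMV data documented. It defines no CMV endpoint at months 6, 9 and 12.
- **The origin of the wording is unknown.** A reader might suppose it was carried over from a trial randomizing at transplantation, or that it is a slip for post-randomization. The article settles neither.
- **Off-visit data may exist.** Table 1 proposes contacts every 3 weeks in months 4 to 6 and monthly in months 6 to 12 post-transplant, and additional visits are permitted. The article also refers to a visit plan that it does not reproduce. A descriptive summary by time since transplantation may therefore be feasible. However, Table 1 is adapted to individual need, and the article does not say which blood tests are done at these contacts or that they reach the eCRF.

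None of this removes the mismatch. The time points are stated, they are on a different clock from the visits, and for some eligible patients they cannot lie within the trial.

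**Conclusion.** The concern holds for the fixed-time incidences of anaemia (including low haemoglobin and use of erythropoietin-stimulating agents) and of low leucocytes and neutropenia. As written, the month-6 and month-9 points precede randomization for later entrants, and most other points miss a study visit.

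The share before randomization rests entirely on the unreported entry distribution. It is 50% and 25% under uniform entry over 12 months, none if all enter within 6 months, and 100% and 50% if all enter after month 6. The poor match to visits depends much less on that assumption, since it exceeds half in every pattern tried, with a ± 21-day window assumed at month 12.

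The consequence is limited. The sample size, the seven-indicator primary endpoint and the named secondary endpoints are untouched, and whole-study incidence from randomization remains valid. The documents do not support a claim of lost follow-up or of a biased safety comparison. This is a stated rule that should be corrected before analysis, and it poses no threat to the trial's main conclusion.

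**What to change.** In the Anemia and Leucocytopenia/Neutropenia sections, define the fixed time points as months 6, 9 and 12 after randomization, that is, visits 3, 4 and 5. Keep the incidence throughout the study from randomization as it is. If a summary by time since transplantation is still wanted, label it descriptive and restrict it to values obtained after randomization.

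For CMV nucleic acid testing, reconcile the stated timing with the visit schedule and state which clock was used. No testing schedule is proposed here. Recruitment has ended, so rewording cannot change when samples already taken were drawn; it can only make clear how they are to be read.

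For the blood-count definitions the cost is wording only, because the visits already exist. The change should be settled before the analysis; the last patient is expected to complete on 30 April 2026.
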